### Randomization and allocation concealment

All eligible participants will be randomly assigned (1:1) to either the pentoxifylline group or the placebo group. The random sequence will be generated by an interactive response technology (IRT) system of a third-party contract research organization (CRO). Drug numbers are marked by personnel independent of the clinical trial. After a subject passes the screening procedure, the IRT will assign the subject a random number that is used to associate the patient with the drug number. This unique drug number will be displayed on the packaging of the study drug assigned to the patient. The random number is associated with the drug and the treatment group by the IRT system. In addition, the IRT could effectively guarantee the implementation of blinding. All participants, primary investigators, healthcare providers, laboratory staff, and statisticians will be blinded until the end of the research. If serious adverse effect occurs, unblinding would be permitted.

### Interventions

All patients will receive standard care of VLUs including compression therapy, sclerotherapy, and endovenous and surgical management. Other standard management such as treatment of infection, debridement, local wound care, anti-inflammatory analgesic drugs, dressings, and metabolic management will be prescribed as appropriate. Current guidelines were followed as per the attending clinician’s judgment [3, 5].

After randomization, participants will be given either pentoxifylline 400 mg twice daily or matched placebo (simulation agent of pentoxifylline) for 24 weeks. Because the dosage of pentoxifylline was 400 to 800 mg per day on the label of pentoxifylline in China, the dose in the trial was 400 mg twice a day. The micronized purified flavonoid fraction (90% diosmin and 10% other flavonoids) is currently one of the most widely accepted effective drugs for CVD and is also recommended by guidelines [17]. Thus, all patients in both groups will be dosed 450 mg diosmin twice daily for 24 weeks. Participants are prohibited from using fibrinolytic drug sulodexide and other venoactive drugs, such as aescin (horse chestnut extracts), coumarins, and low molecular weight heparin. All participants will be required to return the drug tablet to monitor the adherence. There will be no special criteria for discontinuing or modifying allocated interventions.

### Outcomes

#### Primary outcome

Wound healing rate within 12 weeks, expressed as the proportion of participants with complete wound healing of the index ulcer within 12 weeks. Complete wound healing is defined as full epithelialization of the wound without scarring [19].

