In addition, pharmacological treatment could be an option. Venoactive drugs include flavonoids (diosmin), aescin, and coumarins. The main principle of these drugs is to improve venous tone, capillary permeability, lymphatic drainage, and muscle pump function. These drugs could provide relief of pain and swelling or accelerate venous ulcer healing. The nonvenoactive drug sulodexide has also been used to treat VLUs effectively [9]. In recent years, it has been increasingly recognized that chronic inflammation, possibly triggered by sustained venous hypertension, is the principal basis that potentiates the disease progression of CVD. Chronic inflammation of the venous vessel wall could lead to degradation of venous integrity and function, resulting in diminished venous return, fluid accumulation, tissue fibrosis, atrophy, and ulceration in severe cases [10].

Pentoxifylline is used as a drug to treat peripheral artery disease and has been used in the treatment of VLUs. It could inhibit the synthesis of inflammatory mediators, decrease cytokine release, and suppress leukocyte function [11]. The anti-inflammatory effect of pentoxifylline may offer a promising avenue to treat VLUs. In fact, there have been several trials suggesting that pentoxifylline could improve the healing rates of VLUs. In a meta-analysis of 13 randomized clinical trials, pentoxifylline significantly improved the ulcer healing rate and time to healing of VLUs [12].

In addition, other possible mechanisms of pentoxifylline might improve wound healing [13]. Briefly, pentoxifylline could increase cAMP levels in the smooth muscle of vessels, increase erythrocyte flexibility, and then improve microcirculation and oxygen delivery [14]. The fibrinolytic property might degrade microcirculation fibrin, improve skin and subcutaneous nutrition, and then improve wound healing [15].

However, the evidence that currently recommends the use of pentoxifylline in VLUs is relatively weak. Furthermore, none of the trials were carried out in China. Thus, it is imperative to investigate the efficacy and safety of pentoxifylline for VLUs in the Chinese population. Therefore, we designed a multi-center, randomized, double-blinded, placebo-controlled clinical trial to evaluate the efficacy and safety of pentoxifylline in the Chinese population for the treatment of VLUs.

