### Sample size

The aim of this study is to investigate the effect of pentoxifylline on the wound healing rate of VLUs within 12 weeks. According to a recent meta-analysis, the wound healing rates of the pentoxifylline treatment and the control group were 62.7% and 40.6%, respectively [12]. A total of 190 participants will be required at the 5% significance level and 80% power. Assuming a drop-out rate of 20%, 240 participants will be included in this trial.

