### Data analysis

An independent statistical analysis plan will be formulated. All analyses will be conducted in the full analysis set (FAS) population, defined as all patients randomized to an intervention group having at least one efficacy treatment after randomization. The outcomes will also be assessed in the per-protocol set (PPS). The results from FAS and PPS will be compared. Safety set will be used to evaluate the safety of experimental drug. The compliance of treatment and treatment-related withdrawals will be evaluated by arm. Participants’ characteristics and clinical measures will be described as the mean ± standard, median (interquartile range), or frequencies and percentages as appropriate. All statistical analyses will be performed using SAS, V.9.4. All statistical tests are bilateral tests. A *p* value ≤ 0.05 is considered statistically significant.

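### Primary endpoint: complete healing is defined as epithelialization without a scar, so a fully closed ulcer that leaves a scar counts as a treatment failure

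*Protocol article*

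**What the plan says.** The primary measure in the protocol article (Primary outcome) is "expressed as the proportion of participants with complete wound healing of the index ulcer within 12 weeks". The event is then fixed in one sentence: "Complete wound healing is defined as full epithelialization of the wound without scarring". That is a two-part condition: the surface must be fully epithelialized, and there must be no scar. Nothing elsewhere in the article softens the second part or says how a scarred but fully epithelialized ulcer is classified.

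The Secondary outcomes section uses healing at four further time points and restricts recurrence to participants whose index ulcer healed by the 12-week visit. The Analysis of efficacy section adds Kaplan–Meier, log-rank and Cox analyses of healing. None of these gives a separate definition.

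The Sample size section takes its rates from a different source from the one cited for the endpoint. "According to a recent meta-analysis", it says, "the wound healing rates of the pentoxifylline treatment and the control group were 62.7% and 40.6%, respectively". It goes on: "A total of 190 participants will be required at the 5% significance level and 80% power". The Background describes the same source only in general terms: "In a meta-analysis of 13 randomized clinical trials, pentoxifylline significantly improved the ulcer healing rate and time to healing of VLUs". Neither section says what counted as healed in that meta-analysis.

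**The concern.** Eligible ulcers are open wounds of 1 to 20 cm². It is reasonable to expect that such wounds often close with some scar, although the article gives no frequency. The trial's question is whether pentoxifylline helps ulcers to close. A rule that fails a closed ulcer because of its scar answers a narrower question.

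The rule also sets two outcomes against each other. At week 12 an ulcer can show a 100% reduction in area, which is the best possible result on the wound-size outcome, and still be unhealed on the primary outcome.

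Because there is only one definition of healing, the effect spreads. A scarred closure never becomes an event at any healing time point or in the time-to-event analysis. That participant also never enters the recurrence denominator, so a later reopening of the ulcer is not counted. At stake are the number of primary events, the power of the trial and the meaning of the reported healing rate.

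**Working it through.** **Inputs from the protocol article.** Planning rates p1 = 0.627 and p2 = 0.406, 5% significance, 80% power, 190 evaluable, and 240 after a 20% drop-out allowance (Sample size). Two-sided tests: "All statistical tests are bilateral tests" (Data analysis). Equal allocation: "All eligible participants will be randomly assigned (1:1) to either the pentoxifylline group or the placebo group" (Randomization and allocation concealment). Chi-squared or Fisher's exact test, with the result as a risk ratio (Analysis of efficacy).

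**Step 1. The plan's own figure.** With p̄ = (p1 + p2)/2 = 0.5165 and d = 0.221, the pooled formula gives

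n per arm = [1.96·√(2p̄(1−p̄)) + 0.8416·√(p1(1−p1) + p2(1−p2))]² / d² = (1.385 + 0.580)² / 0.0488 ≈ 79.1, that is 80 per arm or 160 in total.

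With continuity correction the total is 176. The stated 190 is not reproduced by any variant tried, but it errs on the safe side: power at 95 per arm is 86.8% (chi-squared approximation) or 83.3% (Fisher's exact). The drop-out step does agree: 190/0.8 = 237.5, against 240 stated. The difference over 190 is a separate matter. It counts here only because it gives the design some slack.

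**Step 2. Model for the scar rule.** Let s be the share of closed ulcers judged scarred. Two assumptions are made that the documents do not supply: the planning rates count any closure, and s is the same in both arms. The literal event rates are then p1(1−s) and p2(1−s).

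- Risk ratio: p1(1−s) / [p2(1−s)] = 0.627/0.406 = 1.54 for every s below 1.
- Risk difference: 22.1·(1−s) percentage points, which shrinks with s.

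**Step 3. Power.** With n per arm and d, p̄, p1 and p2 recalculated at each s, power = Φ{[d − 1.96·√(2p̄(1−p̄)/n)] / √[(p1(1−p1) + p2(1−p2))/n]}.

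Example for s = 30% and n = 95: the rates are 0.439 and 0.284, d = 0.155 and p̄ = 0.362. The two standard errors are 0.0697 and 0.0688, so the argument is (0.1547 − 0.1366)/0.0688 = 0.26 and power is 60%.

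| Share scarred (assumed) | Rates | Difference (points) | Total N for 80% power | Power, 190 | Power, 240 |
|---|---|---|---|---|---|
| 0% | 62.7% vs 40.6% | 22.1 | 160 | 87% | 93% |
| 5% | 59.6% vs 38.6% | 21.0 | 176 | 83% | 91% |
| 10% | 56.4% vs 36.5% | 19.9 | 196 | 79% | 88% |
| 20% | 50.2% vs 32.5% | 17.7 | 242 | 70% | 80% |
| 30% | 43.9% vs 28.4% | 15.5 | 302 | 60% | 71% |
| 50% | 31.4% vs 20.3% | 11.1 | 492 | 41% | 50% |
| 70% | 18.8% vs 12.2% | 6.6 | 934 | 24% | 29% |

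Power crosses 80% at a share of about 9% with 190 evaluable (80.0% at 8.7%, 79.8% at 9%). With 240 analysed it crosses at about 20% (80.2% at 19.5%, 79.8% at 20%). Both columns are relevant: 190 is the planned evaluable number, while the full analysis set with last observation carried forward could keep close to 240 in the primary analysis.

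**The case against.** The strongest reply is that this is one loose qualifier in a condensed article. The definition carries a citation, assessment instructions normally sit in the full protocol or the case report form guide, and the Data collection and management section provides for investigator meetings and training. The trial is also double-blind and reports a risk ratio, which an equal loss of events does not bias. The design has slack as well: about 160 participants would be enough for the planning rates, so a small share of scarred closures would not bring power below target.

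Much of this stands. Missing rater instructions are not a fault of an article, and the slack is why the thresholds are 9% and 20% rather than zero. But the scar condition is not an omitted detail. It is a stated part of the primary event, and if followed it gives the wrong classification. Training sites to apply it faithfully would not help.

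Three stronger readings are tempting, and the documents do not support them.

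- **That the rule pulls the risk ratio towards 1.** Lost events at equal frequency leave it at 1.54. Attenuation would need open ulcers counted as healed as well, and nothing in the plan suggests a route to that.
- **That the definition contradicts the planning rates.** The article does not give the meta-analysis's healing definition, so the most that can be said is that the two are not shown to agree.
- **That some other word was intended, such as absence of scab or drainage.** This is a guess. The article gives no basis for it or for adding such criteria.

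**Conclusion.** Wrong as written. Taken literally, the definition in Primary outcome turns fully closed but scarred index ulcers into failures, there and in every other outcome that depends on healing. That conclusion rests on the text alone.

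The size does not. It depends on an unknown scarring share, on that share being equal in both arms, and on the planning rates counting any closure. Under those assumptions the cost is in events and power, with the risk ratio unchanged: the stated 80% is lost at about 9% scarred with 190 evaluable or about 20% with 240 analysed. A reader might infer from the lower rows of the table that the event rate will collapse. The documents do not show that, because the larger shares are illustrations. Equally, nothing in the documents shows that the share is small enough to ignore.

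**What to change.** - Amend the definition in Primary outcome: full epithelialization (complete closure) of the index ulcer counts as healed whether or not a scar is present.
- State that the same definition applies to healing at 4, 8, 16 and 24 weeks, to the time-to-healing analysis and to the recurrence denominator.
- Instruct all 13 sites before outcome assessments are made. If some have already been made under the present wording, re-classify them while the trial is still blinded.
- In Sample size, confirm that 62.7% and 40.6% use the same healing definition. If they do not, rework the calculation.

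The cost is one amended sentence, a note to the case report form and a check of the cited meta-analysis. No extra visits are needed. Re-classification, if required, adds a blinded review of the records concerned.

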#### Secondary outcomes

The wound healing rate of other periods (4, 8, 16, and 24 weeks)Percent of wound size changes at 12 weeksThe levels of TNF-α and IL-6 at 4, 12, and 24 weeksVenous clinical severity score (VCSS) at 12 and 24 weeksChronic venous insufficiency quality of life score (CIVIQ) at 12 and 24 weeksUlcer recurrence within 24 weeks for subjects whose index ulcer heals by conclusion of 12-week visit

### Follow-up

The total follow-up period is 24 weeks post randomization. The items to be measured and the time window of data collection are shown in Fig. 2.

**Fig. 2 Fig2:**
[figure not shown]
Schedule of enrolment, interventions, and assessments

### Adverse events

All adverse events related to or unrelated to this study, reported spontaneously by the subject or observed by the research investigator, will be recorded. The common terminology criteria for adverse events v5.0 will be used as the criteria of classification of adverse events. Serious adverse events will be reported to the research center expert committee and ethics committee within 24 h. Any adverse event that occurs in the clinical trial will be treated uniformly according to the severity of the adverse event. Follow-up of adverse events will be followed through 12 months after initiation of treatment.

### Sample size

The aim of this study is to investigate the effect of pentoxifylline on the wound healing rate of VLUs within 12 weeks. According to a recent meta-analysis, the wound healing rates of the pentoxifylline treatment and the control group were 62.7% and 40.6%, respectively [12]. A total of 190 participants will be required at the 5% significance level and 80% power. Assuming a drop-out rate of 20%, 240 participants will be included in this trial.

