### Analysis of efficacy

The primary analysis will aim to compare the wound healing rate within 12 weeks between the pentoxifylline group and the control group by chi-squared test or Fisher’s exact test. The result will be expressed as risk ratio and 95% confidence interval. The wound healing rate at 4, 8, 16, and 24 weeks will be assessed by time-event analysis. Kaplan–Meier plot, Log-rank test, and Cox regression will also be used to analysis the time-to-event outcome, with the result of hazard ratio and 95% confidence interval. The covariates that should be adjusted in the Cox regression analysis include gender, age, duration of disease, BMI, pre-treatment ulcer area, compression therapy, and endovenous surgery. Last observation carried forward will be used to fill up the missing values if some primary outcomes may be missing.

The secondary analysis will compare the VCSS score, CIVIQ score, percent of wound size changes, and ulcer recurrence within 24 weeks by *t* test, Wilcoxon rank test, chi-squared test, or Fisher’s exact test as appropriate.

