## Discussion

Pentoxifylline is a readily available, safe, and inexpensive medication that was approved for the treatment of peripheral vascular disease. There were a few of clinical studies supporting a role for pentoxifylline in VLUs. However, the current studies enrolled a small number of subjects and were of short duration. This trial might provide more definite evidence that whether pentoxifylline could be an effective and safe therapeutic option for treatment of VLUs.

VLUs is the most common etiology of lower extremity ulcers followed by peripheral artery disease [4, 20]. It is postulated that the coexistence of both venous and arterial diseases accounted for 26% of patients with lower extremity ulceration [21]. This kind of mixed leg ulcer pose a particular challenge in clinical practice, because they are recalcitrant due to the different underlying pathologies [22]. However, due to the multiple effects of pentoxifylline on both venous and arterial disease, the results of this study might introduce a new choice for mixed arterial-venous ulcers.

Currently, the overall prognosis of VLUs is poor. Although compression therapy is the mainstay of CVD, supplementary therapy might have additional benefit. Combination therapy of venoactive drugs and other medications with different mechanism are usually considered in clinical practice. However, there was little evidence that support combination therapy for VLUs. Because the micronized purified flavonoid fraction (90% diosmin and 10% other flavonoids) is currently strongly recommended in the guidelines of CVD with moderate evidence [1], all subjects will be prescribed diosmin in this trial. The results of this study might provide evidence that whether the combination therapy of diosmin and pentoxifylline could have better effect than diosmin single drug treatment.

In this study, standard of care of VLUs is determined by the treating physicians and not protocolized. This is similar with real world practice. Thus, it is assumed that the results could have good generalization to the general Chinese population.

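### The stated 190 participants at 80% power does not follow from 62.7% versus 40.6%: those inputs need 160 to 182, depending on the test, and 190 gives about 83% to 87% power

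*Protocol article*

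**What the plan says.** The Sample size section of the protocol article takes its planning rates from a meta-analysis: "the wound healing rates of the pentoxifylline treatment and the control group were 62.7% and 40.6%, respectively". It then states the result, "A total of 190 participants will be required at the 5% significance level and 80% power", and the allowance for loss: "Assuming a drop-out rate of 20%, 240 participants will be included in this trial".

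The other inputs are also in the article:

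- The primary outcome is binary, "expressed as the proportion of participants with complete wound healing of the index ulcer within 12 weeks" (Primary outcome).
- Allocation is equal: "All eligible participants will be randomly assigned (1:1) to either the pentoxifylline group or the placebo group" (Randomization and allocation concealment).
- Tests are two-sided: "All statistical tests are bilateral tests" (Data analysis).
- The primary analysis will "compare the wound healing rate within 12 weeks between the pentoxifylline group and the control group by chi-squared test", and the same sentence allows Fisher's exact test as the alternative (Analysis of efficacy).
- No interim analysis is planned (Data collection and management), so no alpha spending raises the number.

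The article states no reduced effect, adjusted alpha, continuity correction or inflation for centres.

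**The concern.** The article gives every input to a two-proportion calculation together with its result, and the result does not follow. A sample-size sentence records what the trial was built to detect and is usually carried into the results report. As it stands, the power, the target difference or the method is misdescribed, or an allowance was made and not mentioned. A reader who repeats the calculation cannot tell which.

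**Working it through.** **Inputs.** p1 = 0.627, p2 = 0.406, difference d = 0.221, mean p = 0.5165. Two-sided alpha 0.05 (z = 1.960), power 80% (z = 0.842), equal arms. Stated result: 190 in total, or 95 per arm.

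**1. Number needed, uncorrected chi-squared (pooled variance under the null).**

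n per arm = [1.960 × √(2 × 0.5165 × 0.4835) + 0.842 × √(0.627 × 0.373 + 0.406 × 0.594)]² / 0.221²

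= [1.960 × √0.49946 + 0.842 × √0.47504]² / 0.04884 = (1.3851 + 0.5801)² / 0.04884 = 79.07

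Rounded up, this is 80 per arm, **160 in total**.

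**2. Other methods at the same alpha and power.**

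| Method | Per arm | Total |
|---|---|---|
| Unpooled variance | 76.34, so 77 | 154 |
| Arcsine | 78.94, so 79 | 158 |
| Pooled chi-squared | 79.07, so 80 | 160 |
| Pooled with continuity correction | 87.89, so 88 | 176 |
| Fisher's exact test, full enumeration | 86 to 91 | 172 to 182 |

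The continuity-corrected value is (79.07/4) × [1 + √(1 + 4/(79.07 × 0.221))]² = 87.89.

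Fisher's test has a range because its power is not monotone in n. Power first reaches 80% at 86 per arm (80.6%) and is 82.1% at 88. It falls to 79.9% at 89 and 90, then is 80.5% at 91. The first size that meets 80% is therefore 172. The size past the dip is 182.

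Converting the two rates to a time-to-event calculation gives about 151 (Schoenfeld) to 161 (Freedman).

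**3. What would give 190.** Among the variants tried at these rates, a one-sided 5% test at 90% power with continuity correction gives exactly 190, and a two-sided alpha of 0.025 gives 192. The first contradicts the stated power and the two-sided tests. The second contradicts the stated 5% level.

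**4. Power at 95 per arm.**

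Uncorrected: z = (0.221 − 1.960 × √(0.49946/95)) / √(0.47504/95) = (0.221 − 0.1421)/0.0707 = 1.116, so power is **86.8%**. Exact enumeration of the chi-squared test gives 86.7%.

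Continuity-corrected: subtracting 1/95 from the numerator gives z = 0.967, so power is **83.3%**. Fisher's exact test by enumeration also gives **83.3%**.

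**5. Difference that 190 detects at 80% power, with 40.6% in the control arm.** About 60.8% versus 40.6% (20 points) by uncorrected chi-squared, and about 61.8% (21 points) with continuity correction. The stated difference is 22.1 points.

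**6. Drop-out step.** 190/(1 − 0.20) = 237.5, which rounds up to 240. In reverse, 240 × 0.8 = 192 evaluable. This step is consistent. The same step applied to 160 gives 200, and applied to 176 gives 220.

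**The case against.** The case for leaving the paragraph alone has several parts.

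**The size of the gap depends on the test.** The plan allows Fisher's exact test as well as chi-squared. Against 160 the stated number is 19% too large (30/160). Against 176 it is 8% too large (14/176), and against 182 only about 4% (8/182). A reader might quote the 19% as the error. The article does not support that as the only figure, because it does not fix the test behind the calculation. This narrows the discrepancy but does not remove it: 190 exceeds the requirement under every method, and power at 190 exceeds 80% under both named tests.

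**An unstated allowance may lie behind 190.** The article condenses a fuller protocol and refers to a separate analysis plan, so a rounded-down effect or a margin may be recorded there. That is possible. The sentence in the article nevertheless presents 190 as the requirement at the stated rates and 80% power, and nothing else in the article alters those inputs.

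**The error does no harm to the trial.** This stands. A reader might infer that the trial is mis-sized or underpowered, or that enrolment must change. The arithmetic points the other way: the number is larger than its own inputs require.

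**A single power of 87% would not describe the planned analysis.** This also stands. Analyses are in the full analysis set, and missing primary outcomes are filled by carrying the last observation forward, so drop-outs may remain in the denominator. As an illustration, assume 120 per arm analysed by chi-squared. If the 20% who drop out are all carried forward as unhealed, the rates become 50.2% and 32.5% and power is 79.8%. If drop-outs heal as completers do, power is 93.4%. The 87% and 83% are therefore the power of 190 evaluable participants at the stated rates, with the test named, and no more than that.

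**Background diosmin.** Both arms receive diosmin, and the Discussion says of adding one drug to another: "However, there was little evidence that support combination therapy for VLUs". A reader might infer that 40.6% is the wrong control rate here. The article does not report the background treatment in the trials behind the meta-analysis, so this cannot be established. It is a separate question from whether 190 follows from the rates given.

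**Conclusion.** The statement is wrong as written. At 62.7% versus 40.6%, two-sided 5%, 1:1 and 80% power, the requirement is 160 evaluable participants (uncorrected chi-squared), 176 (continuity-corrected) or 172 to 182 (Fisher's exact test), not 190. At 190 evaluable, power is about 87% (chi-squared) or about 83% (Fisher's test or continuity-corrected).

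The error is on the safe side. If the assumed rates hold, the primary comparison of 190 evaluable participants has more than the claimed power, and neither alpha nor the drop-out arithmetic is affected. It ranks as a reporting correction. How 190 arose cannot be told from the article.

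The conclusion rests on the stated rates, the two-sided tests, equal allocation and the absence of an interim analysis, all of which the article gives. It also assumes that no further allowance is recorded in a document not shown.

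**What to change.** Keep 240 and correct the sentence in one of two ways, whichever matches what was done:

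- Name the test used for the calculation and give the power that 190 evaluable participants provide at 62.7% versus 40.6%: about 87% for uncorrected chi-squared, or about 83% for Fisher's exact test or the continuity-corrected formula. Say that this refers to evaluable participants.
- Or state the assumption that makes 190 the requirement at 80% power, for example a smaller target difference of about 20 points (uncorrected chi-squared) or about 21 points (continuity-corrected), with 40.6% in the control arm.

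The sponsor's statistician should choose between them from the original calculation. The cost is a change of text, with no change to enrolment, conduct or analysis.
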